## Abstract

**Background:**

The top 3% of frequent attendance in primary care is associated with 15% of all appointments in primary care, a fivefold increase in hospital expenditure, and more mental disorder and functional somatic symptoms compared to normal attendance. Although often temporary if these rates of attendance last more than two years, they may become persistent (persistent frequent or regular attendance). However, there is no long-term study of the economic impact or clinical characteristics of regular attendance in primary care. Cognitive behaviour formulation and treatment (CBT) for regular attendance as a motivated behaviour may offer an understanding of the development, maintenance and treatment of regular attendance in the context of their health problems, cognitive processes and social context.

**Methods/design:**

A case control design will compare the clinical characteristics, patterns of health care use and economic costs over the last 10 years of 100 regular attenders (≥30 appointments with general practitioner [GP] over 2 years) with 100 normal attenders (6–22 appointments with GP over 2 years), from purposefully selected primary care practices with differing organisation of care and patient demographics. Qualitative interviews with regular attending patients and practice staff will explore patient barriers, drivers and experiences of consultation, and organisation of care by practices with its challenges. Cognitive behaviour formulation analysed thematically will explore the development, maintenance and therapeutic opportunities for management in regular attenders. The feasibility, acceptability and utility of CBT for regular attendance will be examined.

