#### **Recruitment**

Regular attenders will be identified from each practice and matched by age, gender and practice to a normal attender to control for practice and socio-demographic characteristics, by practice staff who will write to the patients to request their participation in the study. Approximately 100 regular attenders and 100 normal attenders will be recruited. Pilot work shows that 30-40% of regular attenders will agree to be interviewed but a higher proportion of normal attenders will agree to be interviewed. The representativeness of the selected regular attenders will be compared to the overall sample of regular attenders in the practices and the overall patient lists in terms of age and gender among those aged 18 years or over.

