#### **Procedures and measures**

Practice staff will identify patients who meet the inclusion/exclusion criteria from their primary care practice electronic record. All eligible regular and normal attending patients will be invited to have a baseline interview (see below). Practice staff will send eligible patients a study pack containing an invitation letter (on practice letterhead) inviting them to take part in the study, an information sheet, describing the study, a ‘consent to contact’ form and a stamp addressed envelope. If patients are interested in finding out more about the study and speaking to a researcher, they will be asked to return the ‘consent to contact form’ to the study researcher in the stamped addressed envelope provided. The consent form will also ask the patient’s permission for the researcher to access their anonymised medical records even if they do not wish to be interviewed. A researcher will then telephone the patient to discuss the study further, answer any queries they may have, and if verbal consent is given, arrange a time for interview. One reminder letter (on practice letterhead) will be posted by practice staff to eligible participants who did not respond to the initial invite. In some instances where the GP feels the patient may be suitable for the study but the patient has not responded to invitations to take part, the GP may approach the patient directly and make an appointment to see them to explain the study.

Each patient will be interviewed to explore the presence or absence of psychiatric disorder including depressive disorder, anxiety disorder and somatoform disorder [52] using a structured psychiatric interview (SCID-1) [53], the presence and degree of severity of health anxiety over the last week on the Health Anxiety Inventory (HAI) [24], quality of life on the EQ5D [54], and information on health and social care, work and benefits using the Client Receipt Service Inventory (CSRI) [55] (Table 1).

**Table 1 T1:** Baseline interview

SCID	SCID-1 for DSM-IV (Structured Clinical Interview for Diagnostic and Statistical Manual of Mental Disorders)(First et al., 1997)
CSRI	CSRI Client Services Receipt Inventory (Beecham and Knapp 2001)
EQ5D	EQ5D Standardised instrument for use as a health measurement (Euroqol group 1990)
HAI Short Week	Health Anxiety Inventory (HAI, a 14 item self-rated measure of health anxiety, Salkovskis et.al, 2002) with a score above 21 indicating severe health anxiety.

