We will examine health and social care costs over the preceding 10 years from primary care records in both the regular attenders and normal attenders who have consented to the study. For each preceding year over the last 10 years, information will be collected on the number of contacts and missed appointments with the GP (at surgery, home or telephone contacts), practice nurse, community nurses, counsellors, physiotherapists, occupational therapists, social workers, community workers, NHS Direct, drop-in centres and home help, prescriptions, investigations, secondary care in-patient and out-patient care, and emergency care. Practice based primary care information is likely to be more accurately recorded than contacts that happened outside the practice. However we intend to trawl for the GP referral letters to obtain estimates of secondary care usage and we will also collect contact information for each participant from all local hospitals. Full and complete anonymised data sets of ten year medical records will be processed using a replicable method of electronic data collection that has been developed specifically to answer a number of health and economic and clinically important questions. In addition this data will provide us with a detailed insight into patients resource use in primary as well as secondary care. We will be able to check the data retrieved electronically with the data collected from the modified Client Services Receipt Inventory (CSRI) [55] and therefore check the degree to which care outside the practice may be underestimated. Similarly the analysis of reporting of contacts with primary care at interview compared to the primary care record will explore whether or not regular attenders are underreporting health contacts compared to normal attenders as reported previously [21,51]. To examine agreement in some key information of service use between patient recalls and primary care records, we shall use non parametric correlation analysis which includes Spearman’s rank correlation coefficient, Kendall tau, and Kappa coefficient for different outcome measures where it is appreciated. We will explore the effect any under-reporting by regular attenders may have had on health and social care costs.

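### It is unclear whether patients who allow record access but decline interview enter the 10-year use and cost analyses, and selection is checked only on age and gender

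*Protocol article*

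**What the plan says.** Five places in the protocol article bear on who is in the record-based analyses.

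- **Abstract, Methods/design.** The comparison covers "patterns of health care use and economic costs over the last 10 years of 100 regular attenders" against 100 normal attenders. Interview is not mentioned as a condition.
- **Recruitment (case control study).** "Approximately 100 regular attenders and 100 normal attenders will be recruited". The next sentence reads: "Pilot work shows that 30-40% of regular attenders will agree to be interviewed", and adds that normal attenders will agree more often. Each regular attender is matched to a control on age, gender and practice. The selected regular attenders are then to be compared with all regular attenders in the practices and with "the overall patient lists in terms of age and gender among those aged 18 years or over".
- **Procedures and measures.** The form sent to patients asks for "permission for the researcher to access their anonymised medical records even if they do not wish to be interviewed". The same section says: "Each patient will be interviewed to explore the presence or absence of psychiatric disorder".
- **Statistical analysis in case control study.** The 100 + 100 is justified by 90% power for a difference in depressive and anxiety disorder, which is measured at interview.
- **Health economics in case–control study.** Ten years of costs will be examined "in both the regular attenders and normal attenders who have consented to the study".

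**The concern.** Hypothesis 1 (chronic use for three or more years) and the 10-year cost part of hypothesis 3 can be answered from records. Hypothesis 2 and the EQ5D need the interview. The consent form creates a group with records and no interview, and no later section says what is done with it. The sentence that everyone is interviewed leaves no room for this group. The cost population, defined by consent to the study, could include it.

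Two things are at stake. The first is who the cost and chronicity estimates describe. The health economics section aims at the true cost of regular attenders as a group, but most of them are expected to decline interview, and the two groups will decline at different rates. The second is whether that selection can be seen. Age and gender are two of the three matching variables. Agreement on them does not show that interviewed patients resemble the rest in attendance or cost, and no check is stated for the normal attenders.

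**Working it through.** **1. The plan's own figure.** Inputs from the statistical analysis section: 48% v 25%, 100 per group, two-sided 5%.

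- Pooled proportion 0.365. Null standard error √(2 × 0.365 × 0.635 / 100) = 0.0681. Alternative standard error √((0.48 × 0.52 + 0.25 × 0.75) / 100) = 0.0661.
- Uncorrected power: Φ((0.23 − 1.96 × 0.0681) / 0.0661) = 92.8%.
- With continuity correction (0.23 − 0.01 in place of 0.23): 90.5%. Exact Fisher power: 90.4%.

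The stated 90% reproduces with the corrected or exact test. It belongs to mental disorder, an interview outcome, and says nothing about the precision of costs. It does show that 100 *interviewed* patients per group are needed.

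**2. Three possible readings.**

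| Record-only consenters are | Consequence |
|---|---|
| outside the 100 and left out | costs describe interview acceptors only |
| counted within the 100 | fewer than 100 interviewed per group, so the power in step 1 is not met |
| added for the record analyses | 100 v 100 is not the size of the cost comparison |

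For the second row, if 20 or 30 of each 100 were record-only (assumption), the uncorrected formula gives 86.3% at n = 80 and 81.4% at n = 70, against 92.8% at n = 100. Nothing in the article selects among the three.

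**3. How many regular attenders are not interviewed.** Uptake is 30-40% (Recruitment).

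- Invited for 100 interviews: 100 / 0.40 = 250 to 100 / 0.30 = 333.
- Not interviewed: 150 to 233.

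**4. Possible gain in precision.** The record-only consent rate is not given. Assume 10-30% of those not interviewed.

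- Added regular attenders: 0.10 × 150 = 15 to 0.30 × 233 = 70.
- Fall in that group's standard error: 1 − √(100/115) = 7% to 1 − √(100/170) = 23%.
- Controls: at 50% uptake (assumption; the article says only that it is higher), 100 would not be interviewed and 10 to 30 added. The fall is 1 − √(100/110) = 5% to 1 − √(100/130) = 12%.

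**5. Possible selection.** Let those not interviewed cost *k* times as much on average as those interviewed, and let *r* be uptake. The mean over all invited, relative to the interviewed mean, is *r* + (1 − *r*)*k*.

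| *k* (assumption) | *r* = 0.30 | *r* = 0.40 |
|---|---|---|
| 0.8 | 0.86 | 0.88 |
| 1.25 | 1.175 | 1.15 |
| 1.5 | 1.35 | 1.30 |

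The article gives neither the size nor the direction of *k*. The table shows only that moderate differences would matter and that a check on age and gender would not reveal them.

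**The case against.** A reader might infer that costs are compared only in interviewed patients and that the record-only data are discarded. The article does not say so. The abstract does not make interview a condition, the inclusion criteria require consent to the study and not an interview, and the cost population in the health economics section is worded broadly enough to take in record-only consenters. A condensed article may also leave analysis sets to the full protocol. This stands against any claim of a demonstrated analysis error. It does not remove the ambiguity, because the article itself fixes a sample size, says all are interviewed, and then seeks permission from people who are not.

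A reader might also infer that decliners are the patients most likely to differ. The Background says that people with somatisation are hard to engage in treatment with an overt mental health focus. That makes selection plausible, but it concerns treatment uptake, not research interviews, and gives no direction for cost. Patients who never reply may differ more, and their records are not covered by this permission. On the 10-30% assumption, record-only patients add 6 to 21 percentage points to the 30-40% covered (0.10 × 60% to 0.30 × 70%), so 42-63% of invited regular attenders stay unobserved.

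Two practical objections also stand. Controls accept interview more often, so large equal additions to both groups are not realistic. And the plan matches pairs and conditions its regressions on them, so record-only patients cannot simply be pooled.

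**Conclusion.** The point holds as an ambiguity with a practical consequence. The article seeks record access from patients who decline interview, but does not settle whether they enter the 10-year use and cost analyses. Its only stated check on representativeness cannot detect selection on attendance or cost, at an expected uptake of 30-40% among regular attenders and more among controls.

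Using these patients would reduce the regular-attender standard error by about 7-23% if 10-30% of those not interviewed agree, and the control standard error by less. That consent rate is an assumption, and at its low end the gain in precision is small. The comparison of interviewed with record-only patients is worth having even then, since it gives direct evidence on selection within the limits of who replies.

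**What to change.** 1. In Recruitment and Procedures and measures, state that the 100 + 100 are the interviewed, matched patients who carry the stated power and hypothesis 2.
2. In Health economics, keep the matched comparison, and also run hypothesis 1 and the 10-year costs of hypothesis 3 on everyone in either group who allows record access. Adjust that analysis for age, gender and practice, because the added patients are not pair-matched.
3. Extend the representativeness check: report GP contacts and costs for interviewed and record-only patients, separately in each group.

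The cost is wording and some extra extraction with the electronic method already described. The permission should be confirmed to cover the hospital sources used for costing. The added patients have no interview or CSRI data, so the planned check on under-recorded care outside the practice cannot be made for them. Patients who never reply remain unobserved, and the report should say so.

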**Discussion:**

The health care costs, clinical needs, patient motivation for consultation and organisation of care for persistent frequent or regular attendance in primary care will be explored to develop training and policies for service providers. CBT for regular attendance will be piloted with a view to developing this approach as part of a multifaceted intervention.

## **Background**

In primary care, the top three per cent of face to face attenders with a general practitioner (GP) account for fifteen per cent of all consultations [1]. Frequent attenders (FA) generate five times as many prescriptions and hospital contacts compared to less frequent attenders [2]. Frequent attendance defined as the top 10 per cent of attenders in primary care is discriminative from normal attenders in terms of patient characteristics compared to broader definitions [3]. However, while only one in seven FA (top ten per cent of attenders age and gender adjusted) over one year continue to be FA over the next year, frequent attendance extending over two years usually then persists for a further year [4]. Frequent attendance is more common in some practices than others and varies from doctor to doctor, but most FAs consult all doctors in the practice so a practice based initiative is required to limit and quantify the effects of frequent attendance [5].

Frequent attenders consult practices with medically appropriate problems such as injuries at the same rate as other patients of the same age and gender but they consult more often for other problems such as functional somatic symptoms [6], and mental disorder such as depressive and anxiety episodes [7-15]. Psychological characteristics associated with FA include a history of childhood abuse or neglect and a history of childhood illness exposure (in self or members of family) [13]. Compared to other attenders, FAs have less sense of coherence [16], and greater health anxiety and hypochondriacal beliefs [17,18].

### **Reasons for frequent attendance**

Qualitative studies have thrown some light on the function that frequent consultation serves for the patient. One analysis from the UK suggests FAs have a set of idiosyncratic ground rules for consultation depending on their: perception of the GP’s role (e.g. frequent attendance was justified because the GP was employed to talk to, reassure, help and advise them); 2. relationship with the GP (e.g. less likely to consult so frequently if they thought the GP considered them to be a nuisance or hypochondriacal); 3. perception of their symptoms and past experience and knowledge of them; health anxiety where the fear of consulting outweighed the fear of not consulting; passivity and external locus of control – believing their consulting behaviour and ability to control some of their symptoms was beyond their control; mental health problems such as depression increased consultation behaviour; decision to consult being corroborated by family and friends or having desirable outcomes e.g. quicker return to work; and their familiarity with the processes for gaining access to the GP [19]. The frequency of consultation was much more likely to be increased if several of these factors were present together and less likely to occur if symptoms came under control, if they consulted elsewhere e.g. chiropractor, or if there were changes in life circumstances.

In another UK qualitative study [20], two patterns of consultation were discerned: a larger group who were unaware how frequently they had attended and a second group who related their frequent attendance to a particular crisis in their life that would pass. In general, patients who frequently attended viewed the GP as a respected authority figure who is the most appropriate figure to consult for distinctive and extensive physical symptoms that the patient perceived to require medical care and reassurance. They often described a relatively high number of physical sensations that were difficult for them to endure and required reassurance from their family doctor. Despite holding the doctor in high esteem, most frequently attending patients expressed some dissatisfaction with their treatment, typically in relation to the lack of understanding of their problems by the GP, the lack of an explanation for their problems that they could endorse and the progress made in achieving a resolution of their problems.

In a third qualitative study of frequent attenders with medically unexplained symptoms (MUS) from the United States [21], three groups of patients were identified: 1. patients who despite psychological insight about causes of MUS had neither reduced the intensity of their symptoms nor GP attendance; 2. patients with little psychological insight and capacity to help themselves who had vague symptoms and a strong sense of entitlement to be excluded from normal social roles; 3. patients with high health anxiety and concern that a diagnosis may have been missed who tended to be dissatisfied with their health care and focussed on their symptoms.

Although these quantitative and qualitative studies provide insights to the problems that frequently attending patients face and the conditions under which frequent attendance might occur, they have confounded patients whose frequent attendance is temporary rather than persistent, and they have not systematically linked their findings to opportunities for therapeutic intervention such as cognitive behaviour therapy. For instance the high prevalence of depression and anxiety disorders in these patients is not that informative given that most of these patients have already received and may still be taking antidepressant medication.

A common explanation for increased health care seeking behaviour is the development of health anxiety [22-26], sometimes arising from previous personal or family experience of significant health problems that were not initially diagnosed or managed optimally. Consequently, medical assertions that there is nothing seriously wrong are not reassuring [22]. Health anxiety increases muscle tension that might be experienced as pain and stress related cortisol leading to symptoms such as fatigue, and autonomic overactivity producing symptoms such as palpitations, breathlessness, faintness and diarrhoea. Unless doctors explain and normalise the presence of these symptoms, investment in their importance through investigations, referrals and prescriptions is likely to maintain or increase the health anxiety [27,28].

Another long-standing theory for frequent attendance is somatisation which refers to the presence of somatic symptoms that cannot be adequately explained by organic findings [28]. It tends to be used in relation to MUS, functional somatic symptoms or functional somatic syndromes such as chronic widespread bodily pain or the somatic presentation of underlying mental disorder such as depression presenting as back pain [28]. Somatisation tends to be associated with negative views about mental health, emotional and social issues as being issues of personal weakness and responsibility rather than an issue for health services. The function of somatisation may therefore be blame avoidance and is more common in people who come from families that hold similar views and personal experience involving violation of trust in authority e.g. abuse and not being believed or being helped with abuse [29-31]. For these reasons people with somatisation in any of its forms can be difficult to engage in treatment approaches that have an overt mental health focus leading to poor treatment take up [31,32], and when they are engaged in interventions, frequent attenders in primary care are usually underrepresented e.g. [33].Therefore studies are required that make a particular effort to recruit frequently attending patients in primary care.

### **Intervention studies**

Until recently there was conflicting evidence whether interventions for frequent attenders in primary care improved patient outcomes and reduced healthcare utilisation. Most studies defined frequent attendance over 12 months and in such patients clinical improvement and health care utilisation often improve with standard care over the next 12 months [3]. However, recent trials show evidence of improvement in mental health outcomes and cost effectiveness in patients who were defined as frequent attenders over two years with depressive episodes [34,35] or frequent attenders over two years with MUS [36]. These interventions employed an extensive stepped care intervention involving patient education, antidepressant treatment, monitoring of adherence to medication or nurse delivered antidepressant medication, reduction of analgesics, anxiety management and rehabilitation respectively.

The simplest effective intervention with frequent attenders with somatoform disorders has been the consultation letter [37]. Care within the practice is organised so one lead GP initiates a programme of care for the patient. After a careful clinical assessment involving history taking, physical and mental state examination and investigations, the GP explains that the patient has a problem with “somatisation” where the patient has an excessive focus on their body and becomes worried when there are changes in their body. The GP offers to see the patient on a frequent basis for a limited period to check that this is the case and to gain the patient’s trust. The GP tells the patient that no investigations will be carried out unless new symptoms develop and a physical examination indicates that further investigation is clinically warranted. After four to six weeks, appointments are decreased to monthly then two monthly with the same GP. The practice organises care so all requests for urgent appointments or to see other GPs are discussed with the lead GP and are strongly discouraged unless there is an urgent clinical indication. Randomised controlled trials (RCTs) of this intervention demonstrate reduced health care utilisation and increased physical function in patients who frequently attended with somatisation but have not improved mental health, social function outcomes or the perception that they remain unwell [38,39].

An intensive training course for GPs lasting 15 hours with regular supervision by mental health professionals reduced attendance over one year in a sample of 209 Spanish frequently attending patients [40]. The intervention formulated hypotheses for each patient’s frequent attendance based on organisation of care, doctor-patient relationship, social, cultural, mental or physical health problem grounds.

Although the benefits of a cognitive behaviour therapy intervention are now well established for health anxiety [25,41] and there is some evidence for its benefit in somatisation with frequent attendance [42], it has not been formally tested in relation to helping primary care doctors manage persistent frequent attendance. Despite the identification of reasons for frequent attendance by previous studies, the reasons are not tailored to the needs of the individual patient that the GP is treating. Cognitive behaviour therapy has the potential to formulate specific processes underlying why an individual frequently attends on a day to day basis, and to provide the GP and practice with a tailored plan to manage each persistent frequent attender [43].

